### Randomization

The stratified allocation of the cities (nine cities in each of the three regions) to the intervention groups or to the control group will be performed using a random, computerized allocation procedure. The primary researcher (HM) blindly randomizes the groups for the 27 cities. The safety consultants who execute the face-to-face strategy are assigned by Arbouw.

The intervention and implementation strategy makes blind group assignment of the construction companies, consultants and Arbouw impossible.

### Statistical analyses

The primary outcome measures, i.e. ascertained safety violations, will be presented for the two guidance strategies and the control condition using descriptive statistics. The number of safety violations concerning the installing and use of equipment for working from heights at worksites of painting and maintenance companies ascertained by the Dutch labor inspectorate in the included 27 cities during three weeks in May 2014 will be retrieved by the primary researcher (HM) from the database of the Dutch labor inspectorate. Differences in the mean number of safety violations will be tested using an analysis of variance.

The three process measurements (i.e. satisfaction, insight and safe working behavior) of both intervention strategies are post-tested and converted into continuous variables on a scale of 0–100. The differences between both interventions are examined using independent t-tests.

The analysis is performed on an intention-to-treat basis. IBM SPSS 19.0 will be used for the statistical tests. Statistical significance is defined as p < 0.05 for all outcome measures.

The costs calculation for each intervention strategy will be analyzed descriptively.

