**Methods/Design:**

This study is a block randomized intervention trial in 27 cities to establish the effects of the face-to-face guidance strategy (N = 9), a direct mailing strategy (N = 9) and a control condition of no guidance (N = 9) on safety violations to record by labor inspectors after three months. A process evaluation for both strategies will be performed to determine program implementation (reach, dose delivered and dose received), satisfaction, knowledge and perceived safety behavior. A cost analysis will be performed to establish the financial costs for both strategies. The present study is in accordance with the CONSORT statement.

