## Methods/Design

In a three-armed block randomized controlled trial (RCT), 27 large cities has been stratified within three regions in the Netherlands (North-East, West, South) and each city has been assigned to one of two intervention groups or the control group using nQuery Advisor® Version 7.0. As a result of the inspection procedure of the Dutch labor inspectorate, i.e. unannounced work site inspections in a well-defined area and time period in the Netherlands, the interventions take place at construction companies working in larger cities.

For the description of the design of the safety intervention and the two guidance strategies, we follow the CONSORT statement [13].

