### Sample size

The sample size is based on detecting an absolute difference in safety violations of 25% between the face-to-face guidance strategy and the control condition, and 15% between the direct mail strategy and the control condition. Data from previous inspection projects on equipment for working from heights revealed that in 84% of the cases safety violations were ascertained. We have decided that a 15-25% absolute reduction in ascertained safety violations concerning equipment for working from heights is a realistic and relevant difference.

Based on a power calculation using the nQuery Advisor® Version 7.0, 64 construction locations involved in painting and maintenance per group must be included to achieve a difference of 15% -25% (from 84% to 69% and 59% respectively) with an alpha of 0.05 (two-tailed) and a power of (1-beta) = 0.80. Based on previous inspections on rolling scaffolds, stairs and ladders, the assumption is made that at least half of the construction sites in the 27 large Dutch cities during May 2014 visited by the labor inspectorate are involved in painting and maintenance. Since the policy of the labor inspectorate is not to make a distinction between painting and non-painting companies, this results in a target for the inspections of 128 work sites per group.

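### Cities are randomised, but the sample size and, on its natural reading, the primary ANOVA treat worksites as independent, so the stated 80% power and nominal 5% error hold only without between-city clustering

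*Protocol article*

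**What the plan says.** **Unit of randomisation.** Under Methods/Design, "each city has been assigned to one of two intervention groups or the control group". The Abstract gives nine cities for each of the three conditions, and the Randomization section says that the allocation is stratified, with nine cities in each of three regions.

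**Sample size.** The control rate comes from earlier inspections: "in 84% of the cases safety violations were ascertained". The targeted reductions are "from 84% to 69% and 59% respectively", "with an alpha of 0.05 (two-tailed) and a power of (1-beta) = 0.80". The result is 64 painting and maintenance locations per group. This is doubled to 128 inspected sites per group for one stated reason: about half of the inspected sites are expected to be painting sites. The section gives no ICC and no design effect, and the number of cities plays no part in the calculation.

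**Primary analysis.** The Statistical analyses section takes violations at worksites from the inspectorate's database and then says: "Differences in the mean number of safety violations will be tested using an analysis of variance". It mentions neither a city effect nor a summary per city. It does not say whether region is a factor.

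**Process scores.** For satisfaction, insight and safe behaviour: "The differences between both interventions are examined using independent t-tests".

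**The concern.** When cities are allocated, the arm comparison rests on 27 randomised units, however many sites are inspected in them. If sites in one city resemble each other more than sites in different cities, the variance of an arm mean exceeds what the spread of individual sites suggests. An ANOVA on sites then uses too small an error term, and a sample size based on independent sites overstates the power.

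The protocol gives reasons to expect some resemblance. Companies are recruited around the cities, so one company may have several inspected sites. Some listed hazards, such as the risk inventory and the annual technical examination, may reflect company practice more than the individual site.

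This is the primary test, and the Discussion links a positive result to wider use through the national institute or the labor inspectorate. A false-positive rate above the nominal 5% would bear directly on that decision.

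**Working it through.** **Inputs from the protocol.** 27 cities, nine per arm, three regions. Violation rates 0.84, 0.69 and 0.59. Two-sided alpha 0.05, power 0.80, 64 sites per arm.

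**Assumed.** Between-city ICC of 0.01, 0.05 or 0.10, because the protocol gives none. The same range is used for the proportion (power) and for the number of violations (ANOVA).

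**Step 1: reproduce the 64.** For a three-group chi-square test on independent sites:
- Mean rate = (0.84 + 0.69 + 0.59)/3 = 0.7067.
- Sum of squared deviations = 0.01778 + 0.00028 + 0.01361 = 0.03167.
- Non-centrality per site per group = 0.03167/(0.7067 × 0.2933) = 0.1528.
- At n = 64 the non-centrality is 9.78, and on 2 df the power is 0.806. At n = 63 it is 0.7995.

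So 64 is the smallest n that reaches 0.80. Pairwise formulas under the stated inputs do not give it: 84% v 59% needs 50 (58 with continuity correction), and 84% v 69% needs 125 (138). The calculation therefore leaves no room for clustering.

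**Step 2: design effect.** Sites per city m = 64/9 = 7.11, and DE = 1 + (m − 1) × ICC = 1 + 6.11 × ICC. The effective number per arm is 64/DE, and the power is that of Step 1 at this number.

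**Step 3: type I error of a site-level ANOVA.** With two numerator df and many sites, the rejection rate under the null is approximately 0.05^(1/DE). A simulation checks this: 20,000 null trials, 27 cities, 192 sites, normal outcome.

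| ICC | DE | Effective n per arm | Power (0.806 at ICC 0) | Type I error, 0.05^(1/DE) | Type I error, simulated |
|---|---|---|---|---|---|
| 0.01 | 1.06 | 60 | 0.78 | 0.059 | 0.060 |
| 0.05 | 1.31 | 49 | 0.69 | 0.101 | 0.100 |
| 0.10 | 1.61 | 40 | 0.59 | 0.156 | 0.156 |

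In the same simulation, an ANOVA on the 27 city means stayed at about 0.05 throughout. With unequal city sizes (assumed coefficient of variation 0.6), the site-level error was higher: about 7%, 12 to 13% and 19 to 20%.

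**Step 4: direction of the region effect.** With no city effect and 10% of the variance between regions, an ANOVA that ignores region rejected in 3.5% of null trials. With a city ICC of 0.05 and 5% of the variance between regions, it rejected in 9.1%, against 10.0% without the region variance. Ignoring this balanced stratification factor makes the test more conservative.

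**The case against.** **The article is condensed, and the unit of the ANOVA is not named.** This is fair. Model terms are often left to an analysis plan, and site level is an inference, though the natural one given that the sample size counts locations. The sample size is firmer evidence. It is a finished calculation that assumes independence, and a later analysis plan would not make it right.

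**The size depends on an unknown ICC.** This also stands. At 0.01 the loss is two to three points of power and one point of type I error. The protocol gives no basis for choosing a value.

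**Readings that go too far:**
- A reader might infer that leaving out the region strata also makes p-values too small. Step 4 shows the opposite direction, and the text does not exclude region from the ANOVA.
- A reader might blame clustering for weak power on direct mail. Even with independent sites, 64 per group gives only 52% for 84% v 69%, so that is a separate matter. The protocol's 80% is matched by the three-group test, and that is the figure clustering erodes.
- A reader might suppose that sites in one city share inspectors. The protocol does not say so. Nor need companies lie within one city, since larger companies are recruited because they are expected to work over a wider area.
- A reader might attach an error rate to the process t-tests. The protocol does not say whether workers, employers or company means enter them, and it gives no company or worker numbers from which to compute one.

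The protocol does concede a possible lack of power, but because too few participating companies may be inspected, not because of clustering.

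**Conclusion.** The point holds for city clustering alone. The stated 80% power assumes zero between-city correlation in a trial that randomises cities, and any positive ICC lowers it: to about 78%, 69% and 59% at 0.01, 0.05 and 0.10. If the ANOVA is run on sites, its type I error is about 6%, 10% and 15 to 16% at those values, and more with unequal cities. The effect is minor at 0.01 and material from about 0.05.

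These figures rest on the assumed ICC range, 64 painting sites per arm spread evenly over nine cities, and a normal outcome in the simulation. The error inflation also presumes that variation between regions is not large relative to the city ICC. The powers use a large-sample reference distribution, so a test with 22 residual df would lose a little more.

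**What to change.** **Primary analysis.** State that the city is the unit of inference. Compute one value per city (mean number of violations, and share of painting sites with a violation) and fit arm + region to the 27 values. Residual df = 27 − 1 − 2 − 2 = 22. Alternatively, fit a mixed model to the sites with a random city effect, region as a fixed factor and small-sample df. The two are not identical when city sizes differ, so one should be named in advance. Region belongs in the model because it was a stratification factor: including it gains precision and keeps the error rate correct.

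**Sample size.** Restate the power with the design effect over an ICC range such as 0.01 to 0.10.

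**Process scores (secondary).** If worker-level scores enter the t-tests, use company means for the same reason.

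**Cost.** A change of wording and a restated power; no new data. Confidence intervals widen and the stated power falls. The change corrects the error rate but does not restore the lost power. With nine cities per arm, 80% would take n = 64(1 − ICC)/(1 − 64 × ICC/9) sites per arm: 95 at ICC 0.05 and 200 at 0.10. It is out of reach once the ICC passes 9/64, about 0.14. The report should therefore state the lower power plainly.

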### Hypothesis

We hypothesize that both guidance strategies will reduce safety violations with rolling scaffolds, ladders and stairs compared to the control condition of a general announcement of inspection in construction companies. In addition, the face-to-face strategy is thought to be superior to the direct mail strategy. This is expected to be due to a higher impact of personalized feedback in the face-to-face guidance strategy on executing safety measures within the construction companies compared with awareness-raising in the direct mail strategy. The financial costs are expected to be higher in the face-to-face guidance strategy, especially due to hiring safety consultants and their coordinator for work site visits.

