### Methodological considerations

For both guidance strategies, the content and approach has been developed by the Dutch institute on safety and health in the construction industry. Therefore, the practice base has been incorporated to the maximum. For instance, in the face-to-face strategy, the safety consultants have experience in safety in construction work; in the direct mailing strategy, the information materials have been adapted to the context of painters. In addition, construction companies are free to choose how they want to control the safety hazards when working with rolling scaffolds, ladders and stairs. This adds to the number of dynamic implementation strategies which could also be evaluated in actual performance, i.e. reduced number of safety violations. Standardizing the function and process of complex interventions [18] in this study, respectively stimulating the implementation of safety measures [function] and awareness-raising [process], and personal feedback [process] enables the evaluation of such interventions through RCTs. This method of standardization allows the incorporation of two important elements in studying implementation strategies in pragmatic trials [16,19]: 1) tailoring intervention components to context-specific needs of construction companies, and 2) determining the effectiveness of both strategies on different process measures.

Four categories of process measures are proposed in implementation research in the construction industry [20]: awareness of risk factors and control measures; attitude toward changing behavior; ability to change behavior, and actually changing and maintaining behavior. In the present study, three out of four of these aspects are measured: increase in knowledge in safe working with rolling scaffolds, ladders and stairs, attitude in terms of satisfaction and perceived effect of the interventions, and behavior in terms of the primary outcome measure of safety violations.

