A constraint of this study is that the ability to effect a behavioral change is not explicitly addressed in the interventions and in the process measures, but it is thought that most of the construction workers are able to comply with the safety regulations when working with rolling scaffolds, ladders and stairs. Another constraint is the measurement of safety violations through the inspection procedure of unannounced work site inspections in a well-defined area and time period in the Netherlands. Therefore, a possible lack of power can emerge due to a lack of the intervention companies when the labor inspectorate is inspecting work sites in 18 of the 27 cities. Due to ethical reasons, i.e. introducing unequal risk of incurring financial penalties when safety violations are established by the labor inspectorate, all construction sites in the 27 cities can be the subject of inspection and the researchers will not reveal the names of the 18 intervention cities nor the names of the participating painting companies.

The results of the present study will be available in the second half of 2014.

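### Without the guided share of inspected sites, the arm comparisons mix coverage with effect, and the stated study population contradicts the stated analysis

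*Protocol article*

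**What the plan says.** All references are to the protocol article.

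- **Allocation and recruitment.** Cities are randomized, nine per arm (Methods/Design, Randomization). Companies then volunteer (Recruitment of participants). Setting requires a participating company to work in one of the 18 cities pre-randomized for guidance.
- **Population.** Study population defines it as all sites of the companies that take part.
- **Analysis.** Statistical analyses draws violations from the inspectorate's database for painting and maintenance worksites in all 27 cities, by intention to treat, and says "Differences in the mean number of safety violations will be tested using an analysis of variance". It gives no participation filter and no link to the list of participants.
- **Head-to-head hypothesis.** Hypothesis expects face-to-face to beat direct mail and gives a reason that lies inside the companies: "This is expected to be due to a higher impact of personalized feedback in the face-to-face guidance strategy on executing safety measures within the construction".
- **Scarcity of guided sites.** Methodological considerations concedes that "a possible lack of power can emerge due to a lack of the intervention companies when the labor inspectorate is inspecting work sites". It treats this only as a question of power. The same section counts "behavior in terms of the primary outcome measure of safety violations" among the aspects of behavior change that the trial measures.
- **Uptake.** Process evaluation measures reach as participating companies over invited eligible companies. It also plans dose delivered and dose received among participants.

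**The concern.** Two things do not fit together.

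First, the population and the analysis describe different sets of sites. Control cities have no recruited companies, and a participant found working in one would be a guided company. The population as defined therefore cannot yield the control arm that the analysis needs.

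Second, if the analysis section governs, each intervention arm is a mixture of guided and unguided sites in an unknown proportion. Reach does not supply that proportion: its denominator is invited companies, not inspected sites.

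Two conclusions are then out of reach. A null result could mean that guidance does not work, or that few inspected sites had received it. A difference between the two strategies could come from the strength of personalized feedback, from different coverage, or from both. Coverage could plausibly differ, since one strategy needs one to three agreed meetings and the other is a posted package with web links. The Abstract and the Discussion tie advice on wider implementation to these results.

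**Working it through.** **Inputs from Sample size.** Control rate: "in 84% of the cases safety violations were ascertained". Planned face-to-face effect: "an absolute difference in safety violations of 25% between the face-to-face guidance strategy and the control condition". Planned direct mail effect: "15% between the direct mail strategy and the control condition". The calculation is made "with an alpha of 0.05 (two-tailed) and a power of (1-beta) = 0.80", with 64 painting and maintenance locations per group.

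**The plan's own figure.** A three-group chi-square test (2 df) on 84%, 69% and 59% reproduces it. The mean rate is 0.7067. The sum of squared deviations is 0.03167, and 0.03167 / (0.7067 × 0.2933) = 0.1528. At 64 per group the noncentrality is 9.78 and the power 0.806; 64 is the smallest n that reaches 0.80.

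**Assumptions.** The article gives no coverage figures and no effects per guided site. I assume that (a) the 25 and 15 points hold per guided site; (b) unguided sites stay at 84%, with no spill-over; (c) control cities contain no guided sites; (d) sites are independent. Clustering by city would lower the power further.

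**Model.** Let cF and cM be the guided shares of inspected sites in the face-to-face and mail arms.

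- Face-to-face rate = 0.84 − 0.25·cF
- Mail rate = 0.84 − 0.15·cM
- The expected order reverses when 0.15·cM > 0.25·cF, that is when cM/cF > 25/15 = 1.67

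Power against control at n = 64 is Φ[(d − 1.96·SE0)/SE1], where d is the difference in rates and SE0 and SE1 are its pooled and unpooled standard errors.

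| cF / cM | Face-to-face rate | Mail rate | Order | Power, face-to-face vs control | Power, mail vs control |
|---|---|---|---|---|---|
| 1.0 / 1.0 | 59.0% | 69.0% | as expected | 0.889 | 0.517 |
| 0.5 / 0.5 | 71.5% | 76.5% | as expected | 0.396 | 0.185 |
| 0.3 / 0.3 | 76.5% | 79.5% | as expected | 0.185 | 0.096 |
| 0.3 / 0.5 | 76.5% | 76.5% | tie | 0.185 | 0.185 |
| 0.6 / 1.0 | 69.0% | 69.0% | tie | 0.517 | 0.517 |
| 0.3 / 0.6 | 76.5% | 75.0% | reversed | 0.185 | 0.241 |
| 0.2 / 0.5 | 79.0% | 76.5% | reversed | 0.109 | 0.185 |
| 0.5 / 1.0 | 71.5% | 69.0% | reversed | 0.396 | 0.517 |

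Equal coverage never reverses the expected order. The chance that face-to-face shows the higher observed rate (exact binomial, 64 per arm) is 10% at 1.0/1.0, 23% at 0.5/0.5, 30% at 0.3/0.3, 54% at 0.3/0.6 and 59% at 0.2/0.5.

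These are proportions, because Sample size is written in proportions. The planned test is on mean counts. The same multiplication applies there, but the threshold would be the ratio of the two effects on the count scale, which the article does not give.

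**Could an effect per guided site settle the head-to-head question?** Divide each arm's difference from control by its coverage, treated as known, and subtract. The variance is [0.84·0.16·(1/cF − 1/cM)² + pF(1 − pF)/cF² + pM(1 − pM)/cM²] / 64.

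- At 0.2/0.6 (pF = 0.79, pM = 0.75): variance 0.0963, SE 0.310, 95% half-width 1.96 × 0.310 = 61 points.
- At 0.3/0.9 (pF = 0.765, pM = 0.705): variance 0.0456, SE 0.2135, half-width 42 points.

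The assumed true difference is 10 points. Against control, the estimate at 20% face-to-face coverage has half-width 1.96 × √[(0.1344 + 0.1659)/64] / 0.2 = 67 points.

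**The case against.** The case for the plan has real force.

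- **Intention to treat is legitimate.** Study objectives sets each strategy against control. For a body deciding whether to offer a strategy, uptake is part of the effect. This stands, and the analysis by allocated arm should remain primary. What it cannot support is the mechanism named in Hypothesis.
- **Uptake is measured.** Reach, dose delivered and dose received are planned. All are recorded on invited or participating companies, so none gives the guided share of inspected sites.
- **Study population may imply a match.** If only participants' sites counted, the dilution would disappear in the guided arms. It would leave no control group, and it would need a link that the analysis section does not describe. The supportable statement is that no matching step is described and the two sections conflict. It is not that sites will never be matched.
- **Detail may sit in a fuller document.** A secondary model may well do so, and its absence is no fault here. The conflict over the population is in the article itself.

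A reader might go further and infer that the trial ranks the strategies by uptake, or that direct mail will probably come out ahead. The documents do not support that. The ranking follows coverage times effect, and no coverage figures are given. Recruitment is described once for both strategies, and the article itself expects that guided companies may be scarce at inspection, which sits badly with very high mail coverage. Nor are the 25 and 15 points effects per company: Sample size states them as differences between groups. The analysis section does not specify city-level means either; it names group means and no city summary.

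**Conclusion.** The point holds in this form. As written, the analysis covers all inspected painting and maintenance sites by the city's allocated arm, the defined population is a different one, and nothing planned gives the guided share of inspected sites. A null result is therefore ambiguous, and a difference between the strategies cannot be attributed to personalized feedback.

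The ambiguity is substantial. Under the stated assumptions, two strategies that work exactly as planned at guided sites would be detected against control with power 0.185 and 0.096 at 30% coverage, compared with 0.889 and 0.517 at full coverage. Reversal of the expected ranking needs mail coverage above 1.67 times face-to-face coverage, which is possible but not shown to be likely. All of this rests on assumed coverage, on reading the planned group differences as effects per guided site, and on no spill-over.

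**What to change.** 1. Reconcile Study population with Statistical analyses: state that the primary analysis is intention to treat over all inspected painting and maintenance sites, by the city's allocated arm.
2. After the inspections, have the researchers flag each inspected site in all three arms as face-to-face, direct mail or unguided, using the participant lists and without sight of violation counts. No names go to the inspectorate, so the non-disclosure promised in Methodological considerations is kept. Including control cities matters because Recruitment of participants also targets larger companies expected to work over a wider area.
3. Report the guided share of inspected sites per arm beside the primary result.
4. Without that share, do not credit an arm difference to personalized feedback or a null result to ineffective guidance.
5. Optionally, give a complier-average estimate of each strategy against control, with city-level standard errors, labelled exploratory. It will be very imprecise and does not make the head-to-head hypothesis answerable.

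The cost is a small matching task and a few sentences, with no extra inspections. It assumes that the inspection records identify the company, which the article does not say. That should be checked with the inspectorate first.
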